## Abstract

**Background:**

Poor adherence to medication is one of the limitations in the treatment of cardiovascular diseases, thereby increasing the risk of premature death, hospital admissions, and related costs. There is a need for simple and easy-to-implement interventions that are based on patients’ perspectives, beliefs, and perceptions of their illness and medication.

**Objective:**

The objective is to test the effectivity of this intervention to improve medication adherence in patients with established cardiovascular disease, that is, in secondary prevention.

**Methods:**

In this study the effect of a personalized visualization of cardiovascular risk levels through a website aiming at supporting self management in combination with a group consultation and communication intervention by a nurse on adherence to treatment in 600 patients with manifest cardiovascular diseases will be assessed. The health belief model was chosen as main theoretical model for the intervention.

**Results:**

Primary outcome is adherence to treatment calculated by refill data. Secondary outcomes include the Beliefs about Medication Questionnaire and the Modified Morisky Scale. Patients are followed for one year. Results are expected by 2015.

**Conclusions:**

This study assesses adherence to treatment in a high-risk cardiovascular population by applying an intervention that addresses patients’ capacity and practical barriers as well as patients’ beliefs and perceptions of their illness and medication.

**ClinicalTrial:**

ClinicalTrials.gov NCT01449695; https://clinicaltrials.gov/ct2/show/NCT01449695 (Archived by WebCite at http://www.webcitation.org/6kCzkIKH3)

## Introduction

### Background and Rationale

According to the World Health Organization, almost 50% of all chronic patients do not adhere to their prescribed drug regimen [1]. This is also true for cardiovascular diseases (CVD); only 60% of all cardiovascular patients adhere to their cardiovascular medications (eg, statins, antihypertensives, antithrombotic agents) [2]. This prevalence is similar across all individual CVD medications and occurred in patient who take these medications for primary and secondary prevention of CVD [2]. These figures are startling given that poor adherence results in an increased risk of death in cardiovascular patients [3-5].

Current methods for improving adherence are mostly complex and have limited effectiveness; simple interventions that are easy to implement in daily practice are preferred [6]. Evidence suggests that interventions should be based on the patients’ perspective [7], target patients’ capacity and practical barriers, and address their beliefs and perceptions regarding illness and medication [8,9]. In CVD, life-long adherence is important, and interventions should improve patients’ intentions to take medication as well as solve emergent practical barriers.

These principles were used in the development of the current trial. Specifically, the intervention is based on the health belief model (HBM) [10,11], tailored for the specific purpose of this trial. HBM provides a useful framework for designing behavior change strategies [12]. It is based on the understanding that a person will take health‐related action (eg, being adherent to cardiovascular medication) given four main factors. The first two factors are perceived susceptibility and perceived severity: understanding of the high personal risk and seriousness of a condition (eg, because of the cardiovascular event in the past I am at greater risk for another cardiovascular event). The third factor is perceived benefit, or a belief that a negative health condition can be avoided (eg, being adherent to the cardiovascular medication can help to prevent another cardiovascular event). The last factor is perceived barriers. Cue to action and self‐efficacy and the belief in the ability to successfully undertake the recommended health action (eg, I know how to take my medication on a daily basis) [12,13].

### Trial Design and Aim of the Study

The study will use a single‐center, prospective, randomized controlled clinical trial design and examine the effectiveness of a new intervention that incorporates HBM and behavior change strategies to improve adherent behavior in cardiovascular patients. The intervention consists of a patient-based screening method, a specific nurse-based intervention (structural informative consulting and motivational counseling), and personalized visualization of cardiovascular risk levels via a website. The objective is to test the effectiveness of this intervention to improve medication adherence in patients with established CVD (ie, in secondary prevention).

## Methods

### Study Setting

Participants will be drawn from a hospital‐wide screening program. This screening program is situated at the cardiovascular outpatient clinics in an academic medical center in Nijmegen, the Netherlands. All new patients diagnosed in the last 6 months with acute coronary syndrome, peripheral arterial disease, an aneurysm of the aorta, or stroke/transient ischemic attack (TIA) and referred to the departments of vascular surgery, neurology, or cardiology are automatically included in this program.

### Eligibility Criteria

From this population, participants aged 18 years and older will be selected based on the following inclusion criteria: presence of CVD (acute coronary syndrome, peripheral arterial disease, an aneurysm of the aorta, or stroke/TIA), diagnosed in the last 6 months by a medical specialist, willingness to remain in follow‐up for a period of one year, and provision of signed informed consent. Exclusion criteria are pregnancy (reported by the patient), severe comorbidity (eg, a mental health diagnosis considered by a physician to be a contraindication), problems with the Dutch language (reported by the nurse), or logistic problems such as lack of computer access.

### Intervention

For the intervention, participants will be split in three groups. Participants in group I (control group) receive only usual care. Group II participants receive usual care plus access to a personalized website. For the group III participants, in addition to usual care and access to the personalized website, the intervention program will also include a single group consultation of 60 minutes led by a nurse and a pharmacist followed by two individual consultations of 30 minutes with a nurse.

We want to test if treatment II (only the Web portal) can give the same results as treatment III (the Web portal and the single group consultation followed by two individual consultations). The need for low-cost effective interventions in our health care system led to the motivation for this 3-arm protocol.

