### Sample Size

This study is mainly powered on the primary outcome, the detection of a significant difference between the three degrees of care (usual, additional website, additional counseling) on medication adherence as determined by refill records of computerized pharmacy systems. Based on previous research in our population and data from the literature [26], we estimate that the adherence at the start of the study will be 65% in each group with a standard deviation (SD) of 30%. We hypothesize that the intervention given in group II and the intervention given in group III will result in an increase of 10% in adherence to treatment, resulting in mean adherence rates of 75% and 85% in groups II and III, respectively. To detect these differences in medication adherence the estimated group size with a power of 80% and an alpha of .05 (2‐sided) would be 200 in each group, resulting in 600 participants in total.

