### Statistical Methods

The data will be analyzed based on the intention‐to‐treat principle and evaluated using SPSS, with descriptive statistics (mean, median, SD, and interquartile range) being determined for all variables. The data will be presented in quantitative format (eg, biometrics, laboratory results, blood pressure, lifestyle scores, adherence score on the basis of refill data, and the MMS) and in descriptions of observed effects (eg, change in BMQ, determinants for adherence, evaluation of the use of iVAZ, and appreciation of nurse intervention).

To evaluate the difference between the groups, an analysis of variance test will be performed on the outcome measures for the three patient groups. The independent variable will be the three intervention groups. The dependent variable is medication adherence measured with the dedicated calculation of refill data. Specifically, we will compare the difference between the first and last time-point between groups for the primary and secondary outcomes measures. For the intervention groups II and III, we will also compare the outcomes of the clinical data at 16 and 28 weeks. To correct for multiple comparison, a Duncan’s multiple range test will be performed. Furthermore, we will perform a receiver operating characteristic (ROC) curve analysis to compare the outcome of the screening instruments (MMS and BMQ) with the pharmacy refill dates. In the ROC curve plot, specificity of the questionnaire is on the x-axis and sensitivity of the question is on the y-axis.

Plausible relations between parameters of cardiovascular risk factors, motivation to change, socioeconomic class, and parameters of adherence (calculated refill score and BMQ and MMS scores) will be tested in a univariate manner. Individual parameters will be tested for normality using the Kolomogorov-Smirnov test in order to select adequate univariate tests. Multiple logistic regression analysis will be performed to assess the relative importance of selected parameters for the likelihood of low adherence, as defined by the refill data algorithm. In all analyses, potential confounders will be included if they independently changed the beta coefficient for dedicated calculation of refill data by at least 5% or when consensus about inclusion existed within the team of researchers supported by clinical evidence from literature.

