## Discussion

Nonadherence to medication prescriptions in cardiovascular patients reduces the positive effects of medical treatment in chronic care. However, improvement of medication adherence in these patients is a serious challenge. Patient beliefs, perceptions, and management of medication, their illness (intentional nonadherence), and skills to integrate medication taking in their daily life (unintentional nonadherence) need to be addressed to make an intervention successful.

There is no one‐size‐fits‐all solution for nonadherence [9,34] nor does previous research provide evidence to choose a single intervention [37]. By reviewing the literature it becomes evident that determinants for nonadherent behavior are complex, and underlying theory for a successful intervention is frequently lacking [34,38,39]. In a review of 193 health behavior change articles, only 36% of the authors mentioned a theory and only 22% of them applied the theory [40].

We based our method on HBM, adopted the approach of Horne [41], and defined the main determinants of nonadherent behavior in intentional and nonintentional determinants. Because we address both types of determinants, we expected to develop an intervention that will be more successful than most existing interventions, which only take into account one of these sets of determinants.

Specifically, by choosing a group consultation, information is provided in an efficient manner and the patient is given an opportunity to discuss the need for adherence (intentional nonadherence) as well as getting practical information (unintentional adherence) with peers. Further tailoring the intervention in individual contacts provides the opportunity for the nurse to identify the need to change objectives of unintentional or intentional nonadherence (or a mix of both). These individual consultations are patient‐centered, with emphasis on patient perspectives and shared decision making [42]. The individual website and visualization of personal cardiovascular risk furthermore addresses one of the difficulties in cardiovascular adherence: awareness of the influence of taking medication on personal cardiovascular risk [40]. Lastly, the combination of Web-based intervention with face-to-face contact is expected to give better results than either alone [43]. Based on this integration of factors, we hope that the resulting data of this trial will contribute important knowledge about adherence in this population.

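### The portal-only versus portal-plus-consultations question is worded as sameness, but the trial is powered and tested only for a difference

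*Protocol article*

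**What the plan says.** Four parts of the protocol article bear on groups II (usual care plus portal) and III (the same plus one group and two individual consultations).

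- **Intervention** poses the question as one of sameness: "We want to test if treatment II (only the Web portal) can give the same results as treatment III". The next sentence ties it to the design: "The need for low-cost effective interventions in our health care system led to the motivation for this 3-arm protocol".
- **Sample Size** says the study is mainly powered on "the detection of a significant difference between the three degrees of care". It starts from 65% adherence in each group, "with a standard deviation (SD) of 30" points, and adds 10 points per step, "resulting in mean adherence rates of 75% and 85% in groups II and III, respectively".
- **Statistical Methods** states that "an analysis of variance test will be performed on the outcome measures for the three patient groups", followed by Duncan's multiple range test. The comparison is of change from first to last time-point, by intention to treat.
- **Discussion** says that web-based intervention combined with face-to-face contact "is expected to give better results than either alone".

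The article mentions no equivalence or non-inferiority hypothesis, and it does not say how a non-significant II-versus-III result will be read.

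**The concern.** The reason given for three arms is whether the cheaper portal can stand in for the portal plus nurse time. A yes to that question is a claim of sameness, or at least of not being materially worse. Analysis of variance and Duncan's test can show that II and III differ, but neither can show that they do not. Duncan's procedure also reports means that are not significantly different as one group, a format that invites the wrong reading.

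The practical stake is a decision to offer the portal without consultations. If that rested on absence of significance, it would become easier to reach as the data became noisier or more patients were lost. Under intention to treat, missed consultations would also draw group III towards group II and favour apparent sameness.

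This is more than detail that an article leaves to a fuller document. The question, the powering assumption and the tests are all stated, and they cannot be reconciled without changing one of them.

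**Working it through.** **Inputs.** From Sample Size: SD 30 points, II 75%, III 85%, 200 per group, power 80%, two-sided alpha 0.05. The documents give no margin, so margins below are assumed and shown as a range. Normal approximations are used throughout.

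**The plan's own figure.** For a 10-point difference between two means, n = 2 × [30 × (1.960 + 0.842) / 10]² = 141.3, so 142 per group. The stated 200 is not reproduced, and no dropout allowance is given that would explain it. That is a separate matter. At 200 per group, power for 10 points is Φ(10/3.0 − 1.96) = 91.5%.

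**Precision for III minus II.** SE = 30 × √(2/200) = 3.0 points. The 95% half-width is 1.96 × 3.0 = 5.88 points.

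**Chance of a non-significant result when II is truly worse by d.** This is approximately 1 − Φ(d/3.0 − 1.96), before any multiplicity adjustment:

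| True deficit of II (points) | Non-significant |
|---|---|
| 3 | 83% |
| 5 | about 62% |
| 8 | 24% |
| 10 | 8.5% |

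For two adjacent means Duncan's test works at the nominal 5% level, so it does not materially lower these rates.

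**Sensitivity to the SD and to losses.** The SD of 30 is given for adherence at the start, while the analysis uses change. If the SD is 30 at both times and the correlation between them is r (assumed), the SD of change is 30 × √(2(1 − r)). The last row keeps SD 30 but analyses 142 per arm.

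| Case | SD | SE | Half-width | 5-point deficit non-significant | Margin for 80% power |
|---|---|---|---|---|---|
| r = 0.75 | 21.2 | 2.12 | 4.2 | 34.6% | 5.9 |
| r = 0.50 | 30 | 3.0 | 5.9 | about 62% | 8.4 |
| r = 0.25 | 36.7 | 3.67 | 7.2 | 72.5% | 10.3 |
| SD 30, 142 per arm | 30 | 3.56 | 7.0 | 71% | 10.0 |

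The margin column is (1.960 + 0.842) × SE, for a true difference of zero and one-sided 2.5%.

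**What a formal non-inferiority test would need** (SD 30, true difference zero, one-sided 2.5%). Power at 200 per arm is Φ(margin/3.0 − 1.96); n for 80% power is 2 × [30 × 2.802 / margin]²:

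| Margin (points) | Power at 200 per arm | n per arm for 80% |
|---|---|---|
| 5 | 38% | 566 |
| 7.5 | 70.5% | 252 |
| 10 | 91.5% | 142 |

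**The case against.** The strongest reply is that the sentence in Intervention is not the trial's objective. The Abstract and Trial Design and Aim of the Study state the aim as testing whether the intervention improves adherence. Sample Size, Statistical Methods and Discussion together describe a coherent superiority trial. On this view one loosely worded sentence is the outlier, and it may only mean to ask whether the consultations add anything. This stands in part: it lowers the severity and points to the simplest repair. It does not remove the conflict, because that sentence is tied to the reason for having three arms.

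A reader might go further and infer that the investigators intend to declare equality from a null result. The documents do not support that. They say the trial wants to test whether the results can be the same, not that it sets out to show it, and they contain no rule for reading a null result.

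It is also fair that a null result would not be empty. With SD 30 and 200 per arm, a non-significant result would have an upper 95% limit below about 2 × 5.88 = 11.8 points, and power for the plan's own 10-point step is 91.5%. That still leaves room for deficits of 5 to 8 points, a large part of the assumed step.

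Finally, a margin and an interval rule are often left to an analysis plan. Their absence alone is therefore not the point; the conflict between statements already fixed is.

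**Conclusion.** The point holds as an inconsistency: the sameness question in Intervention cannot be answered by the difference tests in Statistical Methods, and it runs against the 10-point advantage assumed for III in Sample Size and expected in the Discussion. The consequence is a risk of misreading. On SD 30 for the analysed measure and 200 analysed per arm, the interval for III minus II is about ±5.9 points and a true 5-point deficit goes undetected about 62% of the time. The SD of change is not given; over the assumed correlations shown, that figure runs from about 35% to 73%.

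One might also infer that the present size comfortably supports a non-inferiority claim. It does so only for a margin of about 8.4 points or more, which is most of the gain III is assumed to have over II. A 10-point margin would equal that whole gain.

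This should be fixed, but it does not undermine the trial: the superiority comparisons stand as planned.

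**What to change.** **Preferred change.** Reword the sentence in Intervention to ask whether III is superior to II, in line with Sample Size and Discussion. Report III minus II with its 95% confidence interval. State that a non-significant result will not be read as equality. This costs a few lines of text and no patients.

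**Only if a sameness claim is to be kept.** Prespecify and justify a non-inferiority margin clearly smaller than the 10-point step. Make the claim only if the whole 95% interval for III minus II lies below that margin. Add a per-protocol sensitivity analysis beside intention to treat. State openly that, at SD 30, 200 per arm gives 80% power only from a margin of about 8.4 points, with about 70% at 7.5 and 38% at 5. A 5-point margin would need about 566 per arm, so this route is not free of extra patients in general.

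The downside of either route is that sameness becomes harder to claim.

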#### Usual Care (Groups I, II, and III)

All new CVD patients receive the hospital‐wide screening program according to the Dutch guidelines [14] (based on the European guidelines [15]). The screening assesses cardiovascular risk factors in all patients with CVD. It screens for lifestyle risk factors, blood lipid levels, blood pressure, waist circumference, body mass index, blood glucose levels, and a family history of CVDs. Lifestyle is evaluated through a questionnaire which is a compilation of existing validated questionnaires regarding demographic data, smoking, alcohol use, physical activity, and eating habits. For each of these lifestyle issues, the patient’s motivation to change is evaluated [16]. Adherence is measured by the Modified Morisky Scale (MMS) [17] and the Beliefs about Medication Questionnaire (BMQ) [18]. Medication use will be monitored. If necessary and if the patients agree they attend consultations with a nurse based on motivational interviewing to help them lose weight, stop using alcohol, or stop smoking.

According to European guidelines [15], all patients with established CVDs (this means all participants of this trial) should have antiplatelet therapy (eg, aspirin or clopidrogel) and a lipid lowering drug (eg, simvastatin or atorvastatin). The use of antihypertensive drugs is dependent on the systolic blood pressure. Except for the specific additions for the study, all participating and nonparticipating patients receive the same regular preventive cardiovascular care including monitoring of medication use. All patients receive regular vascular care from their medical specialist.

#### Website (Groups II and III)

The website contains an individualized Web portal called Interactive File Vascular Care (Interactive Dossier Vaatzorg, or iVAZ). This is developed to support patient-based self-evaluation and management [19,20]. Patients can log on and see their own cholesterol levels, blood pressure, and lifestyle (smoking habit, exercise, and eating habits) in a risk monitor. Patients can ask questions by email to their nurses, and they can enter changes in their medication. iVAZ provides risk communication, the feedback of clinical outcome will be provided individually, and patients are invited to be active in managing their illness and medication.

#### Group and Individual Consultations (Group III)

For group III, the intervention program will also include a single group consultation of 60 minutes led by a nurse and a pharmacist followed by two individual consultations of 30 minutes with a nurse.

During the group consultations patients receive information about their disease, cardiovascular medication (statins and antihypertensive and antithrombotic agents), and the importance of treatment adherence. Patients will receive an information booklet with all information presented during the plenary session. At the end of this consultation patients are asked to keep a diary of their medication intake during a 2-week period and to set a personal goal for the upcoming individual consultation with a nurse. The group consultation is regarded as an efficient way to increase knowledge and understanding of the risks. It also provides a gathering with other patients (peers).

During individual consultations, the intervention is further tailored based on the goal previously set, patient’s concerns, and necessities using the results of the screening questionnaire (see Data Collection). The following topics will be discussed during the individual consultation: patient's motivation and confidence (barriers, concerns, and positive self-motivational statements about their adherence behavior), options for increasing adherence to treatment, and a global summary of the counseling session.

Both the group and the individual consultations take place at the outpatient clinic. The involved nurses have had training in motivational interviewing [21] and were especially trained for this intervention by a psychologist.

For each of the constructs, we used the recommended behavior change strategies [12,13]. We tailored the intervention further by using the taxonomy of Abraham and Michie [22,23] and the coding manual by de Bruin [24] to categorize the behavior change techniques to be included in the intervention. For each of the components of HBM, the determinants, techniques, and application strategy were developed and are detailed in Figure 1-4.

